#### Adoption

Adoption will be measured on the organisational level in terms of the per cent of sites approached that participate and their characteristics, the number and characteristics of the champions and the withdrawals (site/champion) from the trial and reasons for withdrawal. Characteristics of sites collected will include: organisation, postcode, number of members, staffing and existing programmes offered. At the individual level, adoption will be measured in terms of demographic characteristics of champions and will be collected as part of their pretraining survey. Characteristics captured will include age, gender, caring responsibilities, language spoken at home, Aboriginal and Torres Strait Islander status, NDIS status, work status, health conditions, access to treatment and services and experience/expertise. Data on withdrawals will be tracked by the project team.

#### Implementation

The primary implementation outcome is fidelity of the intervention and training delivery. Fidelity of the intervention across different facilitators and sites will be indexed by fidelity checklists. The lead facilitator and assistant facilitator will both complete fidelity checklists online via Qualtrics at the end of each session, which require them to endorse that each core component of the session has been completed. Checklists will index whether each activity was fully completed, partially completed or not done; whether there were additions or changes to the session and any challenges or issues affecting implementation. They will also request a rating of how confident the facilitator felt for the session, how engaged participants were in the session, whether facilitators approached the session in a manner consistent with the ethos of the programme (eg, holding a space for sharing without resolving or fixing, as well as supporting participants to modify the session to suit their individual needs and to bear witness to stories shared by their peers). Two trial participants will complete a similar checklist which asks whether each activity was fully or partially completed and requests a rating of whether facilitators approached the session in a manner consistent with the ethos of the programme. Accordance between facilitator and participant ratings will be assessed. Our primary fidelity outcome will be the mean proportion of intervention components marked as fully completed, averaged across facilitators, per intervention group.

Fidelity of the training delivery will be indexed by programme assessments which capture comprehension of module content, including a digital portfolio, a statement of practice as a facilitator/boxing coach and a simulated training workshop to demonstrate practical skills.

Semistructured interviews with sites, champions, peer facilitators and participants will be conducted by the research team using questions codesigned by the LEAG. Questions will be designed to explore perceptions among stakeholders, including that the programme and training are agreeable (ie,acceptability), as well as perceived fit and relevance of the programme in the local context (appropriateness). Costs associated with training and programme delivery will be tracked by the research team (sustainability). The barriers and enablers of implementation according to the Consolidated Framework of Implementation Research^69^ will be explored through interviews with sites, champions and participants. Adaptations to programme delivery will be captured through interviews with the site liaison and tracked by the project team. Semistructured interviews with participants and champions will be conducted by the research team in person or via Zoom and will be audio-recorded.

#### Maintenance

Maintenance of programme delivery will be assessed at the organisational level (sites) via interviews with the site liaison, with the primary indicator commitment to ongoing programme delivery at the end of the research funding period. At the individual level (participants), short-term maintenance will be assessed in terms of the effectiveness outcomes at 12 weeks, with maintenance intentions (ie, whether they intend to continue boxing and/or journalling) also captured at postintervention and 12 weeks via surveys.

### Sample size

A sample size of 128 participants (64 participants per arm, clustered into eight groups per intervention arm) would be required to have 80% power to demonstrate superiority of the Left Write Hook over the boxing-only intervention in terms of the primary effectiveness outcome of self-efficacy with a two-sided 5% significance level. This sample size is based on the following assumptions: clinically meaningful absolute treatment difference in mean change from preintervention to postintervention in self-efficacy score of 3 in favour of Left Write Hook (increase), a SD of 5.6 equal in each arm and at each time point (preintervention and postintervention)^70^ and an intraclass correlation of 0.02 to allow for possible clustering effects. Assuming a 15% dropout, a sample size of 150 participants is required (ie, 75 per arm clustered into 10 groups per intervention arm). This sample size represents 0.03% of the estimated number of gender-based violence survivors in the Melbourne population, based on Australian prevalence rates.^71^

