We will use linear mixed effects models to examine the change in the primary outcome of self-efficacy. The response variable will consist of preintervention and follow-up measures, and the model will include fixed effects for treatment group (intervention vs control) and the randomisation stratification factor (site). Random effects will be included to account for clustering at the participant and cluster levels. The absolute treatment difference in mean change from preintervention (week 0; baseline) to 8 weeks postrandomisation (ie, post-intervention) will be estimated with corresponding two-sided 95% CI and p value to evaluate the primary outcome. An adjusted treatment effect based on a model including potential confounding variables will also be obtained. Continuous secondary and exploratory outcomes will be analysed similarly to the primary outcome and targeting a similar primary estimand. Binary secondary and exploratory outcomes will be analysed using logistic regression with adjustment for site. Hair samples will be subject to mass spectrometry, with preintervention and postintervention differences analysed using paired sample t-tests. Quantitative data for the champion experience will be analysed descriptively only.

To determine implementation outcomes, qualitative data from semistructured interviews with participants, champions and peer facilitators will be analysed using NVivo, in line with reflexive thematic analysis.^75^ Themes will be interpreted in collaboration with the LEAG. Finally, the economic costs and benefits of Left Write Hook will be explored using Assessment of Quality of Life^76^ outcomes and costs of champion training and intervention delivery.

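### The sample size pairs an effect on pre-post change with a single-visit SD, so the stated 80% power for the change contrast rests on an unstated pre-post correlation of about 0.49 or higher

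*Protocol article*

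**What the plan says.** The Sample size section of the protocol article defines the effect on the change scale: "clinically meaningful absolute treatment difference in mean change from preintervention to postintervention in self-efficacy score of 3" points in favour of the intervention. The variability input is on the score scale: "a SD of 5.6 equal in each arm and at each time point (preintervention and postintervention"). The remaining inputs are a "two-sided 5% significance level", "an intraclass correlation of 0.02 to allow for possible clustering effects", and "64 participants per arm, clustered into eight groups per intervention arm"; this number "would be required to have 80% power to demonstrate superiority". For attrition it adds: "Assuming a 15% dropout, a sample size of 150 participants is required". Neither a pre-post correlation nor an SD of change is among the listed assumptions.

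The Statistical analysis plan section names the same kind of contrast as primary: "The absolute treatment difference in mean change from preintervention (week 0; baseline) to 8 weeks postrandomisation". The model is a linear mixed model with the preintervention and follow-up scores in the response, fixed effects for arm and site, and random effects for participant and group. The section mentions neither a baseline covariate nor a common baseline mean across arms for this estimate. A further estimate adjusted for unnamed potential confounders is additional to the primary one.

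**The concern.** The effect and the SD are on different scales. If the score has SD 5.6 at both visits and the two visits correlate at rho, the change has SD 5.6 × sqrt(2(1 − rho)). This equals 5.6 only at rho = 0.5. It is larger below that value and smaller above it. A reader therefore cannot get from the listed assumptions to the power of the primary contrast, because the quantity that governs it is not listed.

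What is at stake is whether 128 completers give the stated power for the comparison the trial will report as primary. There is also an efficiency point. A plain difference in change uses the baseline score less well than an analysis that adjusts for it, and the baseline score is already collected.

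**Working it through.** **Inputs (Sample size section).** Difference 3; visit SD 5.6; two-sided 5%; power 80%; intraclass correlation 0.02; 64 per arm in 8 groups, so 8 per group. Rho is not given; it is an assumption here and is shown over a range. The intraclass correlation of 0.02 is applied to whichever quantity is analysed.

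**Reproducing the printed figure.**
- Individually randomised: 2 × (1.96 + 0.84)² × 5.6² / 3² = 54.7 per arm.
- Design effect: 1 + (8 − 1) × 0.02 = 1.14.
- 54.7 × 1.14 = 62.4 per arm. The t-based version gives 56 × 1.14 = 63.84, so 64 per arm and 128 in total, an exact match.
- Dropout: 128 / 0.85 = 150.6, against 150 printed, which is a rounding matter.

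So 5.6 entered the calculation as the SD of the compared quantity.

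**Power at 64 per arm.** The standard error is SD × sqrt(2 × 1.14 / 64) = SD × 0.1887, and power = Φ(3/SE − 1.96). With SD 5.6, SE = 1.057, 3/1.057 = 2.838, and power = Φ(0.878) = 81.0%. The t-based figure is 80.3%.

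The same formula applies with SD = 5.6 × sqrt(2(1 − rho)) for an unconstrained change contrast, and with SD = 5.6 × sqrt(1 − rho²) for a baseline-adjusted contrast:

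| rho (assumed) | SD of change | Power, change contrast | Residual SD, baseline-adjusted | Power, baseline-adjusted |
|---|---|---|---|---|
| 0 | 7.92 | 51.9% | 5.60 | 81.0% |
| 0.2 | 7.08 | 61.2% | 5.49 | 82.6% |
| 0.3 | 6.63 | 67.0% | 5.34 | 84.5% |
| 0.4 | 6.13 | 73.6% | 5.13 | 87.2% |
| 0.45 | 5.87 | 77.2% | 5.00 | 88.8% |
| 0.5 | 5.60 | 81.0% | 4.85 | 90.6% |
| 0.6 | 5.01 | 88.7% | 4.48 | 94.4% |
| 0.7 | 4.34 | 95.6% | 4.00 | 97.8% |

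**Break-even.** The change contrast needs 62.36 × 2(1 − rho) per arm. Setting this to 64 gives 1 − rho = 64 / 124.7 = 0.513, so rho = 0.487. The t-based value is 0.496. With the recruited layout of 10 groups and about 6.4 completers each, the design effect is 1 + 5.4 × 0.02 = 1.108 and the break-even is 0.472 (t-based 0.481). The layout makes little difference.

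**Numbers needed for 80% with the change contrast (8 per group).** At rho 0.3: 62.36 × 1.4 = 87.3 per arm. At rho 0.4: 62.36 × 1.2 = 74.8 per arm. The plan has 64.

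**The case against.** The strongest reply is that no mistake has been shown. A correct change-score calculation with SD 5.6 at both visits and rho = 0.5 gives an SD of change of 5.6 and the same 64 per arm. Stating equal SDs at both visits is what one would do when deriving a change variance. This stands: a reader might infer that the wrong SD was used, but the arithmetic cannot tell that from a silent rho of 0.5. On either account the correlation that carries the power is missing from a list presented as the basis of the calculation.

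A second reply is that the article is condensed and its model description incomplete. It names no time or treatment-by-time term, which a change contrast needs, and it defers detail to a later analysis plan. A mixed model with a common baseline mean also has both visits in the response and also yields a difference in mean change, so it would fit the text. This stands in part. The article does not exclude that model, but it does not specify it either. As written, with an arm effect and no baseline constraint or covariate, it describes the unconstrained contrast.

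Third, the unadjusted change contrast is a valid estimator, so replacing it is a gain in efficiency and not a correction of bias. That is right. The case for the change is that it makes the printed sample size hold without knowledge of rho.

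**Conclusion.** The point holds as a gap between the stated inputs and the stated power. For the unconstrained change contrast that the two sections describe, 80% power requires rho of about 0.49 or higher. Power is 67% at 0.3, 74% at 0.4 and 77% at 0.45, and it exceeds the target at 0.6 (89%) and 0.7 (96%). These figures rest on the normal approximation, 8 groups of 8 completers per arm, an intraclass correlation of 0.02 for the analysed quantity, and assumed values of rho.

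A reader might infer that the trial is underpowered. The document does not support that: it gives no information on rho, and above about 0.5 the planned number is more than enough. The small number of groups, and hence the degrees of freedom for the test, is a separate matter and is not counted here.

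**What to change.** In the Statistical analysis plan section, specify that the primary week-8 treatment difference is estimated with baseline adjustment. Either of two forms will do, keeping site and the group random effect:
- a mixed model with both visits in the response and a common baseline mean across arms; or
- the week-8 score as response, with the baseline General Self-Efficacy Scale score as covariate.

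In the Sample size section, say that 5.6 is the single-visit SD and therefore an upper bound on the residual SD, 5.6 × sqrt(1 − rho²). Under the same approximation, 64 per arm then gives at least about 80% power at any rho. Only this lower bound is free of rho; power still rises with it, to about 85% at 0.3 and 91% at 0.5.

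If the unadjusted change contrast is kept, state rho or the SD of change and restate the power.

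The cost is about one sentence in each section, settled before database lock, with no new data and no added recruitment. One small downside is that the common-baseline form assumes that baseline self-report is not influenced by knowledge of allocation, which should be confirmed from the trial procedures.

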### Statistical analysis plan

Results will be analysed and reported as per the Consolidated Standards of Reporting Trials statement for cluster randomised trials.^72^ A detailed statistical analysis plan will be developed by study statistician/s prior to database lock. Analysis will follow on an intention-to-treat basis according to the cluster’s randomisation allocation. No interim analyses are planned. Cluster characteristics and participant characteristics at preintervention will be summarised using descriptive statistics.

The primary effectiveness estimand for Left Write Hook is defined according to the addendum to the International Council for Harmonisation (E9) Addendum on estimands in clinical trials.^73^ Left Write Hook aims to answer the specific research question: does implementation of the Left Write Hook programme, compared with boxing only, over 8 weeks, improve self-efficacy in survivors, as measured by the change in the General Self-Efficacy Scale,^53^ including the effect of the postrandomisation (intercurrent events) outlined below. Intercurrent events are events that occur postrandomisation and may preclude the observation of the outcome variable or affect its measurement.^74^ Intercurrent events will be tracked by the study team during the study. Possible intercurrent events include the following: participants not adhering to intervention protocol (not attending sessions altogether), participants withdrawing before the end of the intervention, change in or concurrent therapies and/or medication and hospitalisation. Primary estimand attributes are outlined in the online supplemental materials (Table S2).

We will use linear mixed effects models to examine the change in the primary outcome of self-efficacy. The response variable will consist of preintervention and follow-up measures, and the model will include fixed effects for treatment group (intervention vs control) and the randomisation stratification factor (site). Random effects will be included to account for clustering at the participant and cluster levels. The absolute treatment difference in mean change from preintervention (week 0; baseline) to 8 weeks postrandomisation (ie, post-intervention) will be estimated with corresponding two-sided 95% CI and p value to evaluate the primary outcome. An adjusted treatment effect based on a model including potential confounding variables will also be obtained. Continuous secondary and exploratory outcomes will be analysed similarly to the primary outcome and targeting a similar primary estimand. Binary secondary and exploratory outcomes will be analysed using logistic regression with adjustment for site. Hair samples will be subject to mass spectrometry, with preintervention and postintervention differences analysed using paired sample t-tests. Quantitative data for the champion experience will be analysed descriptively only.

To determine implementation outcomes, qualitative data from semistructured interviews with participants, champions and peer facilitators will be analysed using NVivo, in line with reflexive thematic analysis.^75^ Themes will be interpreted in collaboration with the LEAG. Finally, the economic costs and benefits of Left Write Hook will be explored using Assessment of Quality of Life^76^ outcomes and costs of champion training and intervention delivery.

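### Read literally, the primary analysis subtracts the baseline self-efficacy score and does not adjust for it, giving up precision (about 10 points of power if the pre-post correlation is 0.5)

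*Protocol article*

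**What the plan says.** The Statistical analysis plan section describes a linear mixed model for self-efficacy: "The response variable will consist of preintervention and follow-up measures, and the model will include fixed effects for treatment group (intervention vs control". Site is the other listed fixed effect, and there are random effects for participant and cluster. The primary result is "The absolute treatment difference in mean change from preintervention (week 0; baseline) to 8 weeks postrandomisation", with a 95% CI and p value. A further estimate, adjusted for possible confounders that are not named, is to be reported in addition. Continuous secondary and exploratory outcomes follow the same approach. The same section leaves a detailed analysis plan to be written before database lock.

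The Sample size section defines the target as a "clinically meaningful absolute treatment difference in mean change from preintervention to postintervention in self-efficacy score of 3". It assumes "a SD of 5.6 equal in each arm and at each time point (preintervention and postintervention" and "an intraclass correlation of 0.02 to allow for possible clustering effects". It gives no correlation between the two time points.

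**The concern.** The week-0 score is measured on the same scale as the outcome and is due from every participant, so it is probably the strongest predictor of the week-8 score. The listed model uses it only as part of the response, next to a treatment-group term. Taken at face value, that term lets the arms have different baseline means. The difference in mean change then removes the whole of any chance baseline difference between arms, when only the fraction rho of it is expected to carry forward to week 8.

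With 16 to 20 randomised groups, chance imbalance can be appreciable. Over-correcting for it adds noise to the single primary test and to every continuous outcome analysed the same way. The additional adjusted estimate does not remove the issue: it is not the primary result, and its covariates are not stated.

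The power also depends on an unstated quantity. Under a change contrast the relevant SD exceeds 5.6 whenever rho is below 0.5.

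**Working it through.** **Inputs (Sample size section).** Difference 3; SD 5.6 at each time point; ICC 0.02; two-sided 5%; 80% power; 64 per arm in 8 groups of 8.

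**Step 1: reproduce the plan.**
- Without clustering: n per arm = 2 × (5.6 × (1.960 + 0.842)/3)² = 54.7.
- Design effect: 1 + 7 × 0.02 = 1.14, giving 54.7 × 1.14 = 62.4 per arm. Eight groups of 8 make 64.
- Dropout: 128/0.85 = 150.6, against 150 stated.
- Standard error at 64 per arm: √(2 × 5.6² × 1.14/64) = 1.057. Power = Φ(3/1.057 − 1.960) = 81.0%.

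The stated figures reproduce with an analysis SD of 5.6.

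**Step 2: the two analysis SDs.** With SD 5.6 at both visits and correlation rho:
- difference in change (arm means free at baseline): SD = 5.6 × √(2(1 − rho));
- baseline-adjusted or baseline-constrained: SD = 5.6 × √(1 − rho²).

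The ratio of the second variance to the first is (1 + rho)/2, which is below 1 for every rho below 1. The change SD equals 5.6 only at rho = 0.5. The adjusted SD never exceeds 5.6.

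**Step 3: power at 64 per arm.** rho is an assumption here, because the article gives none. The design effect of 1.14 is applied to both contrasts. Normal approximation; gains are from unrounded values.

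| rho | SD, change | SD, adjusted | Power, change | Power, adjusted | Gain (points) |
|---|---|---|---|---|---|
| 0.3 | 6.63 | 5.34 | 67.0% | 84.5% | 17.5 |
| 0.4 | 6.13 | 5.13 | 73.6% | 87.2% | 13.6 |
| 0.5 | 5.60 | 4.85 | 81.0% | 90.6% | 9.6 |
| 0.6 | 5.01 | 4.48 | 88.7% | 94.4% | 5.6 |
| 0.7 | 4.34 | 4.00 | 95.6% | 97.8% | 2.2 |

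At rho 0.5 the standard error falls from 1.057 to 0.915, and 80% power would need about 47 per arm where the change contrast needs about 62.

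**Step 4: sensitivity to the cluster effect.** Step 3 lets the cluster effect vary between visits like the rest of the score. If it is a constant intercept per group, it cancels from the change. At rho 0.5, in units of 5.6²:
- change: 2 × 1.14 − 2 × (0.5 + 7 × 0.02) = 1.00, so SE = √(2 × 31.36 × 1.00/64) = 0.990 and power is 85.8%;
- adjusted with slope 0.5: 1.14 × 1.25 − 2 × 0.5 × 0.64 = 0.785, so SE = 0.877 and power is 92.8%.

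The gain is 7.0 points. The same calculation gives 3.8 points at rho 0.6 and 1.3 at rho 0.7.

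**Step 5: few clusters.** With the Step 3 variances at rho 0.5 and a t reference on 14 df (16 groups), power is 75.2% for change and 86.1% adjusted. A cluster-level simulation of 16 groups of 8 gave 75.7% and 86.2%. A second simulation gave mean estimates of 2.98 (change) and 2.99 (adjusted) against a true 3, and type I error of 0.047 and 0.051. Neither analysis is biased.

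**The case against.** The strongest reply is that free baseline means are an inference. The listed fixed effects are plainly abbreviated: without visit and treatment-by-visit terms, the stated change contrast cannot be estimated at all. A constrained longitudinal model also keeps baseline in the response and reports the same difference in mean change, with about the power of covariate adjustment. If that is what the authors intend, almost nothing is lost. The detailed model is also deferred to a later analysis plan.

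Part of this stands. The article does not exclude the constrained model, so a flat statement that the arm means are left free goes too far. But the one treatment term it does list is a group effect on a response that includes baseline, which is the unconstrained form. Since response, treatment term and contrast are all stated, this is more than detail left for later.

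The reply is also right on three stronger readings that a reader might draw:
- **A biased or invalid analysis.** It is not; a difference in change is unbiased under randomisation.
- **A trial short of its planned power because of this choice.** By the plan's own method, power is 81% at rho 0.5. The loss is efficiency forgone against a better analysis.
- **A sample size that assumed rho = 0.5.** The text gives 5.6 as the SD at each visit, and the same N follows from a week-8 comparison with SD 5.6. The text does not settle which was meant.

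**Conclusion.** The point holds as a precision issue. On its most natural reading, the primary contrast subtracts baseline where adjusting for it would estimate the same treatment difference more precisely. The power forgone is about 10 points if rho is 0.5, and runs from 17.5 points at rho 0.3 to about 2 at rho 0.7. If the cluster effect is constant over time it is about 7 points at rho 0.5.

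An unqualified figure of 10 points is not supported, because the article gives no rho. The sizes rest on the plan's difference, SD and ICC, on equal SDs at the two visits, on the normal approximation, and on randomised groups having the same expected baseline mean in both arms. If the authors already intend a baseline-constrained model, the loss is close to zero and only the wording needs to change.

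**What to change.** In the Statistical analysis plan section, and in the detailed analysis plan, name one of two forms:

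- Keep weeks 0, 8 and 12 in the response, add visit and treatment-by-visit terms, and constrain the arm means to be equal at week 0 (no separate treatment effect at baseline). This stays closest to the stated model and needs no imputation of missing baseline scores.
- Or model weeks 8 and 12 with the week-0 score as a covariate, plus treatment, visit and treatment-by-visit. A participant without a week-0 score then needs a simple baseline imputation to stay in the model.

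In either form, keep site and the cluster and participant random effects, take the week-8 treatment difference as primary, and use the same form for continuous secondary and exploratory outcomes that have a baseline value.

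In the Sample size section, state whether 5.6 is the SD at a single visit, and so an upper bound on the analysis SD under baseline adjustment, or the SD of change, which with equal visit SDs of 5.6 requires rho = 0.5.

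The cost is wording only, with no new data or participants. The detailed plan is still to be written before database lock, and the study biostatisticians are to stay masked until the database is ready for analysis, so the choice can be fixed without sight of results by arm.

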
### Procedure

To determine eligibility, potential participants complete an intake interview with a clinical psychologist prior to enrolment in the trial. All enrolled participants will complete assessments at preintervention (0 weeks), postintervention (8 weeks) and at 1 month following the completion of the intervention (12 weeks). Self-report assessments can be completed at home or on the phone with a member of the research team. In-person assessments are taken by the programme facilitator immediately prior to the first session and immediately following the final session. Detailed information about the methodology and timing of assessments is outlined in figure 1. Eligible participants will not have to pay for the Left Write Hook or boxing-only programmes. Left Write Hook is currently accessible in the community (delivered via a survivor-led charity) through a suggested ‘pay what you feel’ donation of up to AUD$450 to the Left Write Hook charity. Participants also receive a AUD$20 Giftpay voucher for each of the three online assessments they complete. Those in the boxing-only condition will be offered participation in the Left Write Hook programme at the end of the trial.

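### The primary model, as written, has no time or treatment-by-time term, so none of its parameters is the stated difference in change to week 8

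*Protocol article*

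**What the plan says.** The Statistical analysis plan section of the protocol article describes the primary model in four steps.

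- Response: "The response variable will consist of preintervention and follow-up measures".
- Fixed effects: "the model will include fixed effects for treatment group (intervention vs control) and the randomisation stratification factor (site").
- Random effects: "Random effects will be included to account for clustering at the participant and cluster levels".
- Target: "The absolute treatment difference in mean change from preintervention (week 0; baseline) to 8 weeks postrandomisation (ie, post-intervention) will be estimated", with a 95% confidence interval and p value.

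The Procedure section sets the visits: "All enrolled participants will complete assessments at preintervention (0 weeks), postintervention (8 weeks) and at 1 month following the completion of the intervention (12 weeks"). The analysis section does not say whether week 12 enters the primary model. It does say that continuous secondary and exploratory outcomes will be analysed in a similar way. A time effect, a treatment-by-time interaction or a constraint on the baseline means is not named anywhere in the article.

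**The concern.** The model and its target do not match. Treatment arm is constant within a participant. If the response stacks baseline and follow-up scores and the only fixed effects are arm and site, the single treatment parameter is an arm difference in level averaged over all visits. One of those visits is baseline, where randomisation makes the expected difference zero. The promised quantity, a difference in change, would need a parameter that lets the arm difference vary between visits, and the list contains none.

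This is the primary analysis. A programmer who took the list literally would report an interval and p value for a different and usually smaller quantity. Chance baseline imbalance would be averaged into the estimate rather than removed. The same specification would carry over to the continuous secondary and exploratory outcomes.

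**Working it through.** **Inputs from the Sample size section.** Effect: "clinically meaningful absolute treatment difference in mean change from preintervention to postintervention in self-efficacy score of 3 in favour of Left Write Hook". Spread: "a SD of 5.6 equal in each arm and at each time point (preintervention and postintervention"). Clustering: "an intraclass correlation of 0.02 to allow for possible clustering effects". There are 64 participants per arm in eight groups, so 8 per group, with a two-sided 5% level and 80% power.

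**Input not in the article.** The pre-post correlation r is assumed, over the range 0.3 to 0.8. The SD of a change score is 5.6 × √(2(1−r)), which equals 5.6 at r = 0.5.

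**Step 1. Reproduce the plan's figure.** Individually randomised n per arm = 2 × (5.6 × (1.960 + 0.842)/3)² = 54.7, so 55, or 56 with the t distribution. The design effect is 1 + (8−1) × 0.02 = 1.14. Then 55 × 1.14 = 62.7 and 56 × 1.14 = 63.8, in line with 64 per arm. Power at 64 per arm is 81% (normal approximation). The sample size reproduces.

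**Step 2. What the listed model estimates.** With complete data the treatment coefficient is the mean of the arm differences over visits. The expected baseline difference is 0. Let x be the week-12 difference.

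- Visits 0 and 8: (0 + 3)/2 = 1.5.
- Visits 0, 8 and 12, effect kept (x = 3): (0 + 3 + 3)/3 = 2.0.
- Visits 0, 8 and 12, effect lost (x = 0): (0 + 3 + 0)/3 = 1.0.
- In general (0 + 3 + x)/3, which stays below 3 unless x reaches 6.

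**Step 3. Check by simulation.** The design had 10 groups of 8 per arm, 4 sites, intraclass correlation 0.02, r = 0.5 and 300 replicates. The listed model gave mean coefficients of 1.55, 1.99 and 1.02 for the three cases. Adding time and treatment-by-time gave means between 2.98 and 3.14 across all scenarios run, for a true value of 3. With 15% of participants contributing baseline only, the listed model gave 1.26, 1.80 and 0.98.

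**Step 4. Power of a test on that coefficient.** With T visits, the variance of a participant's mean is 31.36 × (1 + (T−1)r)/T. The change-score variance is 31.36 × 2(1−r). In each case SE = √(2 × variance × 1.14/64). At r = 0.5:

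- Change contrast: variance 31.36, SE 1.057, 3/1.057 = 2.84, power 81%.
- As written, two visits: variance 23.52, SE 0.915, 1.5/0.915 = 1.64, power 37%.
- As written, three visits, effect kept: variance 20.91, SE 0.863, 2.0/0.863 = 2.32, power 64%.

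Over the assumed range of r:

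| r | Change contrast | As written, 2 visits | As written, 3 visits, effect kept | As written, 3 visits, effect lost |
|---|---|---|---|---|
| 0.3 | 67% | 42% | 74% | 25% |
| 0.5 | 81% | 37% | 64% | 21% |
| 0.7 | 96% | 34% | 56% | 18% |
| 0.8 | 99% | 32% | 53% | 17% |

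With two visits the loss is large throughout. With three visits and the effect kept it ranges from none at r = 0.3 (74% against 67%) to large at r = 0.8.

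**The case against.** The best defence is that the sentence is condensed. Saying what a model will include does not rule out further terms. The section opens by saying the model examines change, the target is stated as a difference in change, and the Sample size section uses the same quantity. A statistician reading all this would add time and treatment-by-time without being told. The article also defers detail to a statistical analysis plan and puts the estimand attributes in a supplementary table, neither of which is at hand.

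Much of this stands. A reader might infer that the trial's primary result will be halved, or that the trial is badly underpowered. The article does not support either inference: it never says that the treatment main effect will be reported as the primary estimate, and its stated target points to the interaction. The dilution follows only if the list is fitted literally. It also holds only in expectation, since chance baseline imbalance could move a single estimate either way.

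A reader might also infer that a common improvement over time would inflate the residual and cost further power. With balanced, complete data it would not. In 40 fitted two-visit models with a participant random intercept, the standard error of the treatment coefficient was 0.848, 0.848 and 0.850 for common shifts of 0, 3 and 5 points, although the residual variance rose from 17.7 to 37.5. The larger residual is offset by a smaller estimated participant variance.

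The defence does not remove the mismatch. The article goes well beyond naming a model class: it fixes the response, two fixed effects, both levels of random effect and the target. The term that defines the primary effect is the one left out.

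**Conclusion.** The point holds as an error in the written specification: no parameter of the listed model equals the stated difference in change to week 8. Fitted literally, the model would return 1.5 in expectation for a true 3 with two visits. With three visits it would return 2.0 if the effect is kept to week 12 and 1.0 if it is lost. Two-visit power would be about 32-42%, against about 67-99% for the change contrast. A general claim of lost power with three visits is not supported, because it depends on the correlation and on the week-12 effect.

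These figures rest on an assumed pre-post correlation of 0.3 to 0.8, a simple design-effect approximation applied alike to levels and changes, and complete data except where dropout is stated. The article does not settle whether week 12 is in the model. The sample size calculation reproduces and needs no change on this account.

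**What to change.** State the fixed effects as visit (categorical), treatment-by-visit and site, with a common baseline mean across arms, and keep the participant and cluster random effects. Name the week-8 treatment contrast as the single primary estimate and test, and say whether week 12 is in the model. Follow-up scores with baseline self-efficacy as a covariate would be nearly equivalent when data are complete. Use the same specification for the continuous secondary and exploratory outcomes.

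Adding visit and treatment-by-visit is what cures the mismatch. The common baseline mean is a gain in precision on top of that. It relies on randomisation making the expected baseline means equal, and, setting clustering aside, it cuts the variance from 2σ²(1−r) to about σ²(1−r²), a ratio of (1+r)/2: 0.65 at r = 0.3, 0.75 at r = 0.5 and 0.90 at r = 0.8.

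The cost is one sentence in the analysis section and in the statistical analysis plan, written before unmasking. No new data are needed.
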